### Usual care

For patients randomized in both arms, the attending physician will perform the usual clinical examination, and therapeutic treatments will be administered. The choice of drugs and dose will be left to the discretion of the ED physician, as previously reported. Additional analgesia can be administered before, during, or after morphine titration for multimodal pain relief.

### Data collection

Clinical-biological data will be entered in the secure online database of Rouen University Hospital, using Clinsight® software (Ennov Group). The data will be hosted on a secure server located in the Information System Department of CHU-Hôpitaux de Rouen (Rouen University Hospital). Backup copies of the contents of this server are made daily. The data will be entered by the investigator or the clinical study technician of each center, who will have personal and secured accounts (username and password personalized to 6 characters minimum) to access the database of the study. The person carrying out the data processing (biostatistician) will have access to the data once the base has been frozen on a secure server accessible only to the data manager and to the biostatistician of the study.

### Statistical methods

The purpose of this study is to establish the non-inferiority of nebulized morphine titration as compared to IV morphine for relief of severe pain events in adults in the ED. The study is a repeated measures study, measuring pain scores before, during, and after treatment. The desired primary clinical outcome is that nebulized morphine titration is at least as effective in relieving pain as IV morphine 1 h after administration of medication.

In keeping with the non-inferiority nature of the test, a one-sided test at the nominal 0.05 significance level will be performed based on test statistic *z*. This analysis will be complemented by an adjusted analysis based on the linear model in order to adjust treatment comparisons for center and potential factors associated with complete pain relief. In order to obtain 80% power to reject non-inferiority for a 7% margin, and provided there is no difference between true proportions of complete pain relief (i.e., πiv = πae), the required sample size is 404 patients per arm, i.e., 808 patients overall (using software nQuery Advisor, version 6). Owing to the per protocol nature of the main analysis, and in order to account for the possibility of failure to completely or properly administer morphine (i.e., according to planned schedule), the target sample size is 850 patients overall in order to obtain 808 patients in the main per protocol analysis.

Regarding secondary outcome criteria, comparative analyses between the two treatment arms will be performed in an intention-to-treat analysis. Comparisons will be based on Student’s *t* test for quantitative variables, Pearson’s chi-square test for categorical variables, or the logrank test for time-to-event variables.

We will provide a descriptive account of the two treatment groups at baseline in terms of demographics, recruiting center, and baseline values of all study outcomes. All patients and carers will be analyzed according to the group to which they were randomized. No interim analysis is planned.

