## Abstract

**Background:**

Intravenous morphine titration (IVMT) is the French gold standard for opioid treatment in the emergency department (ED). Nebulized morphine titration (NMT) may represent an alternative without venous access, but it has not been adequately studied in adults. We test the hypothesis that NMT is at least as effective as IVMT to initially manage severe acute pain in the ED.

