In the absence of sufficiently robust data, further research on pain in healthy volunteers appears to be an essential prerequisite for a clinical trial on major emergencies. We performed AEROMORPH1 (EUDRACT 2013-001977-26, results in submission process) in order to determine, within a nebulized morphine protocol in healthy volunteers with pain (phase I trial), the pharmacokinetic characteristics and the feasibility of a single 5-min nebulized safety bolus of morphine which could be tested and repeated in the ED.

Given the AEROMORPH1 preliminary data and taking into account the poor results in the literature, we decided to propose the initiation of morphine titration by a new route of administration rather than exclusive NMT. We aim to test the hypothesis that a combined method of morphine titration, initiated by a maximum of 3 nebulized boluses, is at least as effective as IVMT performed exclusively according to the reference protocol for the treatment of patients with severe spontaneous pain (VAS between 70 and 100 mm or NRS ≥ 7/10) in the ED. We decided to perform a multicenter, randomized, placebo-controlled study, a methodological design associated with the highest level of evidence.

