**Fig. 2 Fig2:**
[figure not shown]
Study design

The patient’s pain score will be recorded in the patient’s case report using a Monitoring Sheet (Fig. 3) at time points 0, 5, 10, 15, 20, 25 30, 60, and 120 min by a single investigator. After the end of 180 min of monitoring, the study will be terminated. In arm A, nebulized morphine will be administered with a minimum of 1 and a maximum of 3 5-min boluses of 10 mg (weight < 60 kg) or 15 mg (weight ≥ 60 kg), at 10-min intervals, for 5–25 min. During this period, 1 to 6 IV placebo boluses will be required every 5 min. In arm B, IV morphine will be administered with a minimum of 1 and a maximum of 6 boluses at 5-min intervals (as recommended by the French guidelines on acute pain management [5–7]) for 5–25 min. During this period, 1 to 3 nebulized placebo boluses will be required at 10-min intervals, for 5 min. In both arms, if pain relief is not reached at 30 min (T25 + 5 min), routine IVMT will be performed after validation by the ED physician. No maximum dose will be imposed. The final stopping criteria are the same as previously described.

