## Discussion

This protocol will investigate an alternative route of administration of morphine to reduce the time delay to relief, without losing the benefits of titration. Previously, we had to manage with the poor results reported in the literature. This lack of available data led us to propose first a study protocol based on two different bolus doses of morphine, 10 mg or 15 mg, linked to body weight. According to a recent study [30], the safety of a nebulized bolus of up to 20 mg now seems established, which allowed us to compare these lower doses.

Regarding the primary endpoint of our study, we will measure the main outcome at 1 h for both pharmacokinetic and ethical reasons. First, this outcome is the same as that of our large study on IVMT in the ED [12] with the objective of complete relief, related to VAS ≤ 30/100 or NRS ≤ 3/10. This previous study established that when IVMT is performed in the ED for spontaneous severe acute pain, the median number of boluses expected is 3 (95% confidence interval (CI), 3–4), but with a range between 1 bolus and more than 10 boluses [12]. Moreover, our study protocol is original given the “combined” design of arm A, which means that IVMT is not a rescue procedure but a real part of the protocol, before this main outcome endpoint at 1 h (IVMT begins at 30 min). The objective is to replace only the first 5 IV boluses of morphine, not to replace or shorten the entire IVMT. Evaluating criteria during the titration process should be avoided. Our primary outcome at 1 h is a consequence of these pharmacokinetic considerations. Secondly, this evaluation at 1 h seems to be ethically acceptable in case of failure.

Incidentally, our study protocol shows many differences with the Grissa et al. study [30], such as the shorter duration of the aerosol application, a time lapse without treatment (5 min), and in the control group, a standard of care that conforms more to the French learned society recommendations with IVMT doses adjusted to weight ≥ 60 kg. Finally, the Grissa et al. study aimed for a 50% reduction in pain intensity, while we preferred to target total pain relief, but with combined titration. We chose an endpoint with the same delay, but we chose to perform a non-inferiority trial to study the complete relief of severe acute pain using this new combined NMT + IVMT method of titration.

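### The stated claim is non-inferiority of nebulized morphine, but the 1-hour comparison supports it only for nebulized titration followed by IV titration

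*Protocol article*

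**What the plan says.** The protocol article states the claim in two ways.

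- **Nebulized alone.** Statistical methods gives the purpose as to "establish the non-inferiority of nebulized morphine titration as compared to IV morphine", and continues: "The desired primary clinical outcome is that nebulized morphine titration is at least as effective in relieving pain as IV morphine 1 h after" dosing. The abstract says: "We test the hypothesis that NMT is at least as effective as IVMT to initially manage severe acute pain in the ED". The abstract's methods paragraph then defines NMT as one to three nebulized boluses, with no IV morphine in the definition.
- **Combined.** The Background hypothesis concerns "a combined method of morphine titration, initiated by a maximum of 3 nebulized boluses", compared with IV titration performed exclusively. Study aims and the description of arm A under randomization say the same. The Discussion stresses that in arm A "IVMT is not a rescue procedure but a real part of the protocol".

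The primary endpoint is VAS ≤ 30 or NRS ≤ 3 at 1 hour. Under Study protocol, in both arms, "if pain relief is not reached at 30 min (T25 + 5 min), routine IVMT will be performed" once the ED physician validates it, with no maximum dose. Usual care adds: "Additional analgesia can be administered before, during, or after morphine titration for multimodal pain relief". The abstract and the randomization section place the start of routine IV titration after 25 minutes. Study protocol and the Discussion place it at 30 minutes.

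Relief at 30 minutes is a secondary outcome. Secondary categorical outcomes are compared by Pearson's chi-square test in the intention-to-treat population, and no margin is given for them.

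**The concern.** A non-inferiority result is reported in the words of its stated purpose. Here those words attribute the result to nebulized morphine, while the 1-hour reading follows up to half an hour of the same IV titration in both arms. That shared treatment pulls the arms together, so a shortfall of the aerosol shows at 1 hour only in reduced form. A difference small enough to pass at 1 hour could come from a larger difference at the end of the nebulized phase.

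Relief at 30 minutes is the last reading before shared IV titration (if that starts at 30 minutes). A chi-square p-value alone does not say how large a deficit remains compatible with the data, and a non-significant result there could be misread as equivalence. At stake is what the trial may conclude about a route of administration meant to spare venous access.

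**Working it through.** **1. The plan's own figure.** Inputs from Statistical methods: margin 0.07, one-sided 0.05, 80% power, equal true rates, 404 per arm. The common relief rate p is not given, so solve for it from n = (1.645 + 0.842)² × 2p(1 − p) / 0.07². With p = 0.80 this gives 403.8, rounded up to 404. With p = 0.79 it gives 419 and with p = 0.81 it gives 389. The size therefore implies 80% relief at 1 hour, and that value is used below.

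**2. What an inert aerosol would cost.** The Discussion says "the median number of boluses expected is 3", with a range from 1 to more than 10. Assume boluses-to-relief are lognormal with median 3, F(k) = Φ(ln(k/3)/σ), scaled so that arm B reaches 80% at 1 hour. With boluses every 5 minutes, arm B can have 12 before 1 hour (minutes 0 to 55) and 6 by the 30-minute reading (minutes 0 to 25). An arm A patient with an inert aerosol has 6 effective boluses if IV titration starts at 30 minutes, or 7 if it starts at 25. Relief after k boluses is 0.80 × F(k)/F(12).

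The upper tail is assumed three ways: 97.5th percentile at 8 boluses (σ = ln(8/3)/1.960 = 0.500), 97.5th percentile at 10 (σ = ln(10/3)/1.960 = 0.614), and 90th percentile at 10 (σ = ln(10/3)/1.282 = 0.939).

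| Tail | Relief after 6 | 1-h loss, 30-min start | Relief after 7 | 1-h loss, 25-min start |
|---|---|---|---|---|
| 97.5th = 8 | 73.6% | 6.4 | 76.6% | 3.4 |
| 97.5th = 10 | 70.5% | 9.5 | 74.2% | 5.8 |
| 90th = 10 | 66.2% | 13.8 | 70.2% | 9.8 |

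Relief after 6 boluses is also arm B's relief at 30 minutes, so with about 0% in arm A the 30-minute gap is about 66 to 74 points. With the 30-minute start, the 7-point margin is 7/13.8 = 51% to 7/6.4 = 109% of the nebulized phase's whole 1-hour effect.

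**3. Would it pass?** P(pass) = Φ((0.07 − gap)/SE − 1.645), where SE = √[pA(1 − pA)/404 + 0.80 × 0.20/404]. For the first row with the 30-minute start, SE = 0.0296 and (0.07 − 0.0643)/0.0296 − 1.645 = −1.45, so P = 7%. The other two rows give 0.7% and about 0%. With the 25-minute start the three rows give 34%, 11% and 0.5%.

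**4. A partly active aerosol.** Assume that a share r of patients unrelieved at 30 minutes is relieved by 1 hour in both arms. Then the 1-hour gap = the 30-minute gap × (1 − r). The 7-point margin corresponds to a 30-minute gap of 7/(1 − r): 10 points at r = 0.3, 14 at r = 0.5, 23 at r = 0.7. With r = 0.5:
- 60% against 50% at 30 minutes becomes 80% against 75% at 1 hour, and passes with probability 17%.
- 60% against 53% becomes 80% against 76.5%, and passes with probability 33%.

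**5. Precision at 30 minutes.** With 404 per arm, a two-sided 0.05 chi-square has about 51% to 65% power to detect a 7-point deficit for assumed IV rates of 0.40 to 0.80. A 90% interval for the risk difference would have a half-width of 1.645 × √[2p(1 − p)/404]: 5.8 points at p = 0.50 and 4.6 points at p = 0.80.

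**The case against.** The strongest reply is that the trial's hypothesis is the combined strategy. Background, Study aims and the arm descriptions say so. The Discussion defends the 1-hour reading on pharmacokinetic and ethical grounds and argues against judging efficacy while titration is under way. On that reading the nebulized-alone wording is shorthand and the endpoint is sound. This stands as to the endpoint. It does not cure the wording, because the abstract defines NMT without IV morphine and the analysis section is where the purpose of the test is fixed.

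A reader might go further and infer that the trial cannot detect a useless aerosol and would declare it non-inferior. The documents do not support that. The test needs the confidence limit, not the point estimate, inside 7 points. At 404 per arm and 80% relief the observed gap must be no more than about 7 − 1.645 × 2.81 = 2.4 points (2.81 being the standard error in points). An inert aerosol would usually fail, and the planned 30-minute comparison would expose a gap of 66 points or more. Time to relief, total dose and relief by exclusive NMT would add information.

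Two further limits are fair. Thirty minutes is free of shared IV titration only if that starts at 30 minutes, and it is not free of co-analgesia, which is permitted before and during titration. A gated 30-minute non-inferiority test at 7 points would have only about 64% to 80% power for assumed rates of 0.40 to 0.80. Counting permitted co-analgesia as failure would bring the discretion of clinicians who may not be blinded into the outcome. Neither is a required change, and an analysis plan not shown here may already set a 30-minute margin.

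**Conclusion.** The concern holds as a mismatch between the claim and the comparison. The 1-hour endpoint is valid for nebulized-then-IV titration against exclusive IV titration. It does not isolate nebulized titration, which is what the abstract's hypothesis and Statistical methods say will be shown.

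Under the assumed distributions, the nebulized phase's whole contribution at 1 hour is about 6 to 14 points, or 3 to 10 with the earlier IV start, against 66 to 74 points at 30 minutes. An inert aerosol would pass in fewer than 8% of trials with the 30-minute start and in up to 34% with the 25-minute start. A partly active one could pass more often.

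These sizes rest on the lognormal shape and tails, the back-solved 80%, no relief at 30 minutes from an inert aerosol, and boluses given on schedule. Waiting for the physician's validation would mean fewer boluses and a larger 1-hour loss. The mismatch itself rests on none of these assumptions. It should be corrected because it governs what the trial may conclude.

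**What to change.** 1. In the abstract's hypothesis and in Statistical methods, restate the purpose and permitted conclusion as titration started by nebulized morphine and continued intravenously, compared with exclusive IV titration.
2. Report relief at 30 minutes as a risk difference with a confidence interval, not a chi-square p-value alone. State that a non-significant result there is not equivalence, and that no claim about nebulized morphine itself will be made unless a 30-minute margin was pre-stated. Note beside the result that co-analgesia was allowed.
3. Reconcile the start of routine IV titration: after 25 minutes in the abstract and randomization section, 30 minutes in Study protocol and Discussion. The choice decides whether the 30-minute reading precedes shared IV treatment.

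The cost is wording and one re-expressed analysis of data already collected. The price is a narrower permitted claim, and precision at 30 minutes is limited.

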#### Subject selection and inclusion criteria

Criteria for eligibility are adult patients, 18–75 years of age, presenting to the ED with a primary complaint of spontaneous severe acute pain who are being considered for admission to the ED observation unit whatever their pain etiology. An episode of severe pain is defined as the occurrence of pain that is rated 70/100 or more on the VAS (0–100), and when the VAS evaluation is impossible, pain that is rated 7/10 or more on the NRS (0–10). The VAS handheld slide rule will be shown and explained to the patients. When patients have difficulties in manipulating the VAS slide rule, nurses will be allowed to use the NRS (from 0 to 10), as these two scales are equivalent in the ED [5]. All nurses in the ED have been trained to assess pain using these unidimensional scales. A second VAS or NRS measurement will be taken in the examination room, to confirm the first measurement of severe acute pain recorded in the ED. If this second measurement confirms VAS ≥ 70/100 or NRS ≥ 7/10, the investigator will check the inclusion and exclusion criteria for enrollment.

Patients will be screened consecutively 5 days per week (Monday to Friday) during the day, when the organizational conditions for enrollment are met, until the sample size of 850 patients is reached. Patients cannot be consecutively enrolled in the study because high inflow or high workload in participating EDs is an obstacle, and is difficult to predict. Patients will be included when the study coordinator or a dedicated team member is available for enrollment and when a single examination room is available for treatment.

Inclusion and exclusion criteria are presented in Table 1.

**Table 1 Tab1:** Inclusion and exclusion criteria

Inclusion criteria	
• Age ≥ 18 and < 75 years	
• VAS ≥ 70/100 or NRS ≥ 7/10	
• Patient affiliated with or beneficiary of a social security category	
• For women (childbearing age)	
○ Effective contraception (oral contraception, intrauterine device or use of condoms)	
○ Menopausal status (amenorrhea less than 12 months before the inclusion visit)	
○ Objectivized sterility (diagnosis or surgically)	
Exclusion criteria	
• Chronic pain (> 3 months)	
• Taking opioids more than 10 days (including opioids as tramadol and/or codeine)	
• Taking opioids in the emergency room within 4 h	
• Taking rifampicin	
• Impaired ability to discern, cognitive impairment	
• Morphine-related contraindications	

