### Outcome parameters

The primary outcome of this study is complete pain relief, related to the final VAS (0–100 mm) or NRS (0–10). The primary endpoint is the relief rate defined as VAS ≤ 30/100 or NRS ≤ 3/10 at 1 h from the beginning of titration.

Secondary outcomes are to compare all the parameters of analgesic efficacy for each method of titration and to evaluate the feasibility and tolerance of the nebulized route of morphine administration.

Analgesic efficacy will be measured by assessing the total dose of morphine administered (based on weight and body mass index (BMI)), the median delay of relief, the proportion of patients relieved according to the duration of titration (pain relief at 30 min and 120 min from the start of titration), and the proportion of patients totally relieved by exclusive NMT. Feasibility will be evaluated by measuring the rate of deviation from the protocol (major and minor; see Table 2). For side effects, we will record the incidence of respiratory depression, the incidence of sedation by the Ramsay score [44, 45], and the incidence of vegetative minor side effects associated with opiates (nausea, vomiting, urinary retention).

**Table 2 Tab2:** Morphine titration protocol deviations

Error	Effect	Deviation
RR not taken 1 time	Underestimated	Minor
RR not taken at least 2 times	Underestimated	Major
RR < 12 and bolus done	Underestimated	Major
RR > 12 and bolus stopped	Overestimated	Major
Uncoded SpO2	Underestimated	Minor
Uncoded Ramsay	Underestimated	Major
Continued at Ramsay > 2	Underestimated	Major
Uncoded side effects	Underestimated	Minor
Side effects and bolus pursuit	Underestimated	Major
Too high dose, weight < 55 kg	Overestimated	Major
Too high dose, weight 55–60 kg	Overestimated	Minor
Too low dose, weight 60–65 kg	Underestimated	Minor
Too low dose, weight > 65 kg	Underestimated	Major
Stopped at 35 ≤ VAS < 40 not related to side effects	Underestimated	Minor
Continued at VAS ≤ 25	Overestimated	Minor
Started at 65 ≤ VAS ≤ 70	Overestimated	Minor
Stopped at VAS ≥40 not related to side effects	Underestimated	Major
Continued at VAS ≤ 20	Overestimated	Major
Started at VAS ≤ 60	Overestimated	Major
Time between bolus 5 < *T* ≤ 7 min	Underestimated	Minor
Time between bolus 3 ≤ *T* ≤ 5 min	Overestimated	Minor
Time between bolus > 7 min	Underestimated	Major
Time between bolus < 3 min	Overestimated	Major
Nebulized bolus dose # 10 or 15 mg	Exclusion	Major
IV bolus dose # 2 or 3 mg	Exclusion	Major

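### Free improvement, not an error: the non-inferiority decision could use the risk difference adjusted for the time-0 pain score instead of the unadjusted z test

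*Protocol article*

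**What the plan says.** All references are to the protocol article.

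- **Deciding analysis (Statistical methods).** "a one-sided test at the nominal 0.05 significance level will be performed based on test statistic" z, in the per-protocol set. No covariate is named.
- **Adjusted analysis (same section).** "This analysis will be complemented by an adjusted analysis based on the linear model". It adjusts for centre; beyond that, the article speaks only of "potential factors associated with complete pain relief", without a list. The analysis has a supporting role, and entry pain is neither named in it nor excluded from it.
- **Sample size (same section).** "In order to obtain 80% power to reject non-inferiority for a 7% margin". The calculation takes the true relief rates in the two arms as equal. The result is 404 per arm (808), with 850 to be enrolled. The common relief rate is not stated.
- **Endpoint (Outcome parameters).** Success is a fixed cut-off on the 1 h score: at most 30 on the VAS, or at most 3 on the NRS.
- **Entry (Subject selection and inclusion criteria).** "pain that is rated 70/100 or more on the VAS". Where the VAS cannot be used, the NRS equivalent applies.
- **Conduct (Study protocol).** Pain is scored at time 0. Titration continues to the same threshold that defines success, and no maximum dose is imposed.
- **Randomisation.** Stratified by sex and centre, not by entry pain.

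**The concern.** The endpoint asks for a larger fall from patients who enter with more pain. If entry pain predicts relief at 1 h, part of the patient-to-patient variation in the outcome is explained by a value measured before treatment. An unadjusted comparison leaves that part in the standard error. The trial is sized for 80% power against a 7-point margin, so a smaller standard error at no cost is worth having. The plan already contains an adjusted model, but as a complement it cannot change the decision. Two things are open to improvement: which of the two planned analyses decides, and whether the time-0 score is fixed as a covariate of the one that does.

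**Working it through.** **1. The plan's own figure.** The inputs from Statistical methods are one-sided alpha 0.05 (z = 1.645), 80% power (z = 0.842), a margin of 0.07 and equal true rates. Solving for the unstated relief rate:

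p(1 − p) = 404 × 0.07² / [2 × (1.645 + 0.842)²] = 1.9796 / 12.37 = 0.160, so p = 0.80 (or its mirror, 0.20).

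Forward: n = (1.645 + 0.842)² × 2 × 0.80 × 0.20 / 0.07² ≈ 404 per arm. Rates of 0.79 and 0.81 give 419 and 389. The stated size is therefore that of an unadjusted test at 80% relief. That rate is an inference, and everything below assumes it.

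**2. Fall needed to succeed.** Entry score minus 30: 70 − 30 = 40 mm at the lowest entry score, 100 − 30 = 70 mm at the highest.

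**3. Effect of adjustment.** Let R² be the share of outcome variance explained by the entry score. Approximately:

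SE = √[2 × 0.16 × (1 − R²) / 404], and power = Φ(0.07/SE − 1.645).

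With R² = 0, SE = 0.0281 and power = 80.0%. The equivalent saving in patients is about 808 × R².

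**4. Values of R².** The documents give none, so these are assumed models. All have entry scores uniform on 70–100 and 80% relief overall.

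| Assumed fall in VAS by 1 h | R² | Power | Patients of 808 |
|---|---|---|---|
| Fully proportional to entry, SD 30–40% of entry | 0.004–0.007 | 80.2–80.3% | 3–6 |
| Half-proportional (mean fall rises 0.5 mm per mm of entry), SD 40 mm | 0.006 | 80.2% | 5 |
| Half-proportional, SD 25 mm | 0.014 | 80.5% | 11 |
| Independent of entry, SD 40 mm | 0.022 | 80.8% | 18 |
| Independent of entry, SD 25 mm | 0.053 | 81.9% | 43 |
| Independent of entry, SD 15 mm | 0.125 | 84.5% | 101 |

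In the SD 25 mm independent case, relief is about 92% for entry below 75 and 65% for entry above 95. The last row needs relief to drop from about 96% to 56% between those bands. If entry pain and relief were unrelated, R² and the gain would both be zero.

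**5. The same on the margin scale.** The distance from the estimate to the one-sided 95% limit is 1.645 × 0.0281 = 4.63 points unadjusted. At R² = 0.053, SE = 0.0274 and the distance is 4.51 points, a gain of 0.12 points.

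**6. Check by simulation.** This used 20,000 trials of 404 per arm and compared an unpooled z test with a linear model adjusted for entry score with robust standard errors. In the SD 25 mm independent case, power was 79.8% unadjusted and 81.6% adjusted. At a true 7-point deficit, across the cases simulated, the rejection rate was 4.8–5.3% unadjusted and 4.9–5.2% adjusted. Adjustment did not inflate the type I error.

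**The case against.** The case for leaving the plan alone is strong in several respects.

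- **The test is valid.** A comparison of two proportions needs no covariate under randomisation, and the sample size matches it. This stands. A reader might infer that the primary analysis is wrong or the trial underpowered, but the arithmetic above shows neither.
- **An adjusted analysis is already planned.** Its open covariate list may include entry pain, and an SAP may name it. This also stands. The open list is not a fault in itself in a condensed article. What the article does fix is that the unadjusted test decides.
- **Titration to target weakens the link.** Patients with more pain can receive more boluses, there is no dose cap, and sleeping patients count as relieved. It is tempting to say that the endpoint depends on the entry score by construction. Only the required fall does. Whether relief at 1 h depends on it is an empirical matter that no section reports. Titration need not remove the link, because the endpoint is read at a fixed 1 h and IV boluses come at 5-minute intervals. The Discussion also cites a range of 1 to more than 10 boluses in the earlier IV titration study.
- **The gain is small.** In most of the assumed models it is under one power point. A reader might notice that 43 patients nearly equals the allowance of 850 − 808 = 42. That is a coincidence of one assumed SD, and the allowance covers per-protocol losses, not imprecision.
- **Chance imbalance in entry pain is not an extra bias.** The unadjusted standard error already allows for it, so it should not be counted as a second harm.

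**Conclusion.** The point holds as a missed efficiency. The deciding test leaves out a baseline value that is collected anyway and that sets how far each patient must fall to succeed. The benefit is real if entry pain predicts relief, but probably modest: power of about 80.2–82% instead of 80%, or about 3 to 43 of 808 patients. A figure of 84.5% requires a strong dependence that uncapped titration to the same threshold makes less plausible. These sizes rest on an inferred 80% relief rate, uniform entry scores and assumed models for the fall in pain, none of which the documents supply. The reason to act is that the change costs almost nothing, not that the present plan fails.

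**What to change.** In Statistical methods (or the SAP), before database freeze:

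- Base the non-inferiority decision on the adjusted risk difference, from a linear model with robust standard errors or a logistic model standardised to a risk difference.
- Name the time-0 pain score as a fixed covariate, on one scale (VAS, or NRS × 10).
- Declare non-inferiority if the lower one-sided 95% bound of the difference (nebulised-first minus IV) lies above minus 7 points.
- Keep the unadjusted z test as a sensitivity analysis.

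The cost is one or two sentences. The margin, its scale, the sample size and the data collected stay as they are.
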